##### Stage 3: Preparation

In the sixth week, a list of problems and difficult situations related to gaming will be provided for the adolescents to consider to prevent relapse. The adolescents will also write out different approaches for controlling online gaming and give a score of 1 to 10 out for all approaches presented. They will then choose an approach with respect to implementation and achievability.

##### Stage 4: Action

In the sixth week, adolescents will be encouraged to consider obstacles that may disrupt their plans. The adolescents will be asked to consider approaches to prevent them from being tempted to game online. Motivational videos will be provided to enhance adolescents’ confidence and motivation to perform better.

Factors that lead to maintaining good behavior and helping adolescents to achieve their goals are addressed at the beginning of the seventh session. Regarding the choice of a healthy lifestyle as a measure to prevent addiction to online games, it will be suggested that alternative behaviors could be tried such as having a sports program instead of going to gaming clubs, connecting with friends and attending parks and cinemas in groups, stress management training, and relaxation techniques.

##### Stage 5: Maintenance

In the seventh week, a worksheet of enjoyable activities will be provided to adolescents to prevent them from being tempted to play online games. Motivational videos will also be presented to enhance efforts to maintain their new behaviors. To enhance decisional balance, adolescents will receive information on the consequences of online games (both positive and negative consequences) including physical, mental, and emotional impacts in shorter and longer terms. In order to reduce stress and improve adolescents’ self-efficacy, training in relaxation techniques including body relaxation, breathing relaxation, yoga (as an audio file), mindfulness training, and mental imagery will also be used in the HAPPYTEEN app.

##### Active control condition

Eight educational sessions on “sleep hygiene” will be performed for the participants in the active control group. Sleep hygiene intervention was chosen for the control group based on a recent study on the targeted sample [1]. This study found that insomnia is prevalent among Iranian adolescents, and it can affect adolescents’ quality of life. Moreover, it was found that IGD severity was significantly associated with insomnia. Therefore, this intervention will be conducted to help adolescents in the active control group increase their quality of life and mental health.

The sleep hygiene condition includes video, text, and audio files that explain each section. In each training session, the purpose of that session and the previous content will be reviewed, and by providing complete explanations, the following content will be taught: sleep hygiene, study of sleep habits, sleep management, identifying incorrect patterns of behavior related to sleep and the impacts of environment, time, physical activity, and nutrition on sleep. The details of the intervention for the active control group are shown in Table 3.

**Table 3 Tab3:** Intervention content for the active control group

Sessions	Content
First session	Introducing the program and aims of the training sessions, familiarity with the sleep process, scientific definition of sleep and sleep hygiene, studying the mechanisms of sleep and wakefulness, the effects of sleep on body organs and quality of life
Second session	A review of the contents of the previous session, the effect of sleep on the body, familiarity with the body's biological clock, the relationship between sleep cycle and wakefulness with age and normal sleep time during the day
Third session	Review of the contents of the previous session, review of sleep stages and NREM and REM cycles and review of changes in this cycle on body organs
Fourth session	A review of the contents of the previous session, review of sleep disorders, statistics on the prevalence of sleep disorders, definition of insomnia and characteristics of people with these disorders
Fifth session	Review of the contents of the previous session, review of sleep-disturbing factors such as identifying and modifying environmental factors affecting sleep patterns (e.g. sound, bed quality, temperature, etc.)
Sixth session	A review of the previous session, review of other factors that disrupt sleep, the relationship between nutrition and modification of eating habits with the benefit of adequate sleep, familiarity with the effect of exercise on experiencing good sleep
Seventh session	Review of the previous session, identifying and considering pre-sleep habits, the impact of technology on sleep, mentations and solutions to improve sleep
Eighth session	A summary and review of the sessions

### Sample size/power calculation

The sample size for the study was estimated based on a pilot study of 12 adolescents with IGD. The results of the pilot study showed that adolescents reported lower scores on the IGDS-SF9 at post-treatment follow-up (pre-treatment *M* = 34.59, *SD* = 16.91; post-treatment *M* = 25.37, *SD* = 17.94). However, 2 adolescents did not complete the post-treatment assessments. It is hypothesized that the app-based intervention will have at least a moderate mean effect size of 0.50 (Cohen’s *d*) compared to the control group. Using G*Power [61], sample size was calculated assuming a power of 90% for a two-group comparison analysis with three measures over time, the significance level of 0.05 and loss to follow-up of approximately 20%. The final sample size was set at 103 participants for each group.

### Assessments and outcomes

#### Data collection methods

Data collection from demographic information to measuring the severities of Internet Gaming Disorder (IGDS-SF9), insomnia (ISI), and depression, anxiety and stress (DASS-21), determining the status of the adolescents in stage of change in the TTM model (SOCQ), the degree of self-efficacy and decision-making balance in adolescents will be done with an online questionnaire. At the beginning of the study, participants will be assured that their information is and will remain confidential within the research team. Figure 2 provides a SPIRIT depiction of the schedule of enrollment, interventions, and assessments.

**Fig. 2 Fig2:**
[figure not shown]
SPIRIT figure: schedule of enrollment, interventions, and assessments

#### Sociodemographic variables

Demographic questions will include information on participants’ age, gender, educational level, type of school, parents’ education, type of gaming device (console, personal computer, cellphone, etc.), and duration of using online games in weekdays and weekends. This information will be collected by an online questionnaire.

##### Primary outcome measure

The primary outcome measure will be the IGDS-SF9. The IGDS-SF9 assesses the severity of IGD in adolescents [6, 62]. These activities include any game, whether online or offline performed through consoles, computers, laptops, tablets, and smartphones. The IGDS-SF9 has 9 items correspond to the nine IGD criteria defined by the DSM-5. All items are rated a five-point Likert type scale from 1 (never) to 5 (always). The total score is obtained by summing all 9 responses and range from 9 to 45 with higher scores indicating a higher risk of developing IGD. The Persian version of the *IGDS-SF9* was found to be highly valid and reliably among Iranian adolescents [62].

##### Secondary outcome measures

Secondary outcome measures will include the Depression, Anxiety and Stress Scale (DASS-21), Insomnia Severity Index (ISI), Stages of Change Questionnaire (SOCQ), Decisional Balance Scale, and Self-efficacy Scale.

##### The Depression, Anxiety, and Stress Scale (DASS-21)

To assess stress, anxiety, and depression in adolescents, the DASS-21 will be used [63]. The DASS-21 is a 21-item self-reported measure that consists of 3 subscales of stress, anxiety, and depression. Each subscale includes 7 items, and each item is rated on a four-point Likert type scale from 0 (did not apply to me at all) to 3 (applied to me very much, or most of the time). The subscale scores can be computed through the sum of the 7 responses and range from 0 to 21, with higher scores indicating greater anxiety, stress or depression. The validity and reliability of the Persian version of the DASS-21 was found to be acceptable in previous studies [64, 65].

##### Insomnia Severity Index (ISI)

The ISI is a brief self-reported instrument that measures adolescents' perceptions regarding the severity and the effects of insomnia. The ISI consists of seven items that are rated on a five-point Likert scale from 0 (no problem) to 4 (very severe problem). The total score is obtained by summing all 7 responses and the score ranges from 0 to 28 where 0–7 indicates absence of insomnia, 8–14 indicates subthreshold insomnia, 15–21 indicates moderate insomnia, and 22–28 indicates severe insomnia [66]. The Persian version of the ISI was found to be valid and reliable among both clinical and general populations of Iranians [67].

##### Stage of Change Questionnaire (SOCQ)

Stage of change will be measured using a single item: “Did you play online games for 20 hours or more a week during last month?”. Reponses options are as follows: “A. Yes, and I do not plan to reduce my digital game use. B. Yes, and I plan to reduce my digital game use in the next 6 months. C. Yes, and I plan to reduce my digital game use in the next 30 days. D. Not this month, but I have played digital games for less than 20 hours a week in the past 6 months. E. No, and I have not played digital games more than 19 hours a week in the past 6 months. F. No, and I have NEVER played digital games more than 19 hours a week”.

Based on the answers given, the participants will be classified into one of the five stages of change described in the present study: A = (Precontemplation), B = (Contemplation), C = (Preparation), D = (Action), E = (Maintenance), and F = (A participant that is unlikely to be struggling from IGD) [58].

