### Study interventions

#### Intervention condition

The TTM model consists of six domains including (1) stages of change, (2) process of changes, (3) decisional balance, (4) change level, (5) self-efficacy, and (6) temptation. In this study, we will focus on three domains, as described below. The first domain is stages of change. While changing behavior and achieving the desired behavior, it is important to consider different stages [27]. In the first stage (Stage 1: Precontemplation), due to lack of awareness or knowledge or experiences of failed attempts to change in the past, the person may not have enough motivation to consider behavioral change during the next 6 months. In the next stage (Stage 2: Contemplation), the person has the necessary knowledge regarding the results of performing the desired behavior and knows the benefits of performing the behavior and the costs of performing the behavior, but he/she may not have self-confidence or motivations to make changes in behavior during the next 6 months. In the third stage (Stage 3: Preparation), people may analyze more fully costs and benefits in performing the behavior. People in this stage value the benefits more than the obstacles, and by planning for the next 30 days, they typically feel one step closer to their goals. After the preparation stage, the person may be better able to resist temptations and persevere to adopt the new behavior. In the next stage (Stage 4: Action), a new behavior may be adopted by the person within the next 6 months. In the next stage (Stage 5: maintenance), positive changes in his/her lifestyle have typically occurred, and he/she has experienced a change in behavior for at least 6 months and a maximum of 5 years with more confidence and less temptation. The risk of unusual temptations and the consequences of false self-confidence may still precipitate relapse.

The second domain of the TTM model involves processes of changes. These processes include overt and covert activities that a person may use to progress through the stages of change. In other words, these include any activities that a person does to help modify the way he/she thinks, feels or behaves.

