### Statistical analysis

A blinded biostatistician will analyze the data using SPSS version 25 and MLwiN version 2.27 software. An intention-to-treat analysis will be used to compare the intervention effects between the active control and intervention groups. The Kolmogorov–Smirnov test will be used to assess normality distribution of study variables. Multilevel linear models (MLMs) using a random-effects model will be conducted to compare primary and secondary outcome measures across the two groups over baseline and at 1 month and 3 months after the intervention. Within-group intraclass correlations will be calculated, and a two-level mixed model will be used with adolescents nested in time.

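### As printed, the stage-of-change item does not separate Action from Maintenance, and its categories are assigned to a linear model

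*Protocol article*

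**What the plan says.** The protocol article, under Stage of Change Questionnaire (SOCQ), measures stage with a single item whose stem is "Did you play online games for 20 hours or more a week during last month". Options A, B and C all answer yes and differ only in the intention to reduce. The other three are these:

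- The option coded as Action reads "D. Not this month, but I have played digital games for less than 20 hours a week in the past 6 months", with the contrast placed at its start.
- The option coded as Maintenance reads "E. No, and I have not played digital games more than 19 hours a week in the past 6 months", which opens with a plain denial.
- The remaining option, which stands for no stage, reads "F. No, and I have NEVER played digital games more than 19 hours a week".

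The mapping of these three is "D = (Action), E = (Maintenance), and F = (A participant that is unlikely to be struggling from IGD". The same section says that "the participants will be classified into one of the five stages of change described in the present study", although six options are mapped and F is not one of the five.

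Under Intervention condition, a person in Maintenance is one of whom it is said that "he/she has experienced a change in behavior for at least 6 months". The SOCQ is listed under Secondary outcome measures. The Statistical analysis section states: "Multilevel linear models (MLMs) using a random-effects model will be conducted to compare primary and secondary outcome measures across the two groups". It makes no exception for the SOCQ.

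**The concern.** Movement between stages is the first specific aim listed under Objectives. Stage is also one of the three transtheoretical-model domains that the trial sets out to study, and the Discussion says the app is meant to carry adolescents towards action and maintenance. The item therefore has to register one transition above all: from 20 or more hours a week to fewer. If the Action and Maintenance options describe the same history, and neither clearly describes someone who has recently cut down, the outcome is least reliable where an effect of the app would show.

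The analysis adds a second difficulty. A linear model needs a numeric score with meaningful distances. Five ordered stages do not supply such distances, and an option outside the ordering has no position on the score at all.

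**Working it through.** No figure in the protocol needs reproducing here. The check compares the options as printed with every relevant playing history, then compares the assessment times with the six-month window.

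**Inputs.** The item stem, options A to F and their mapping come from the SOCQ section. The abstract gives 2 months of sessions. The Intervention condition section places the questionnaires at baseline and at 1 and 3 months after the intervention ends.

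**Step 1: D against E.** Both deny 20 or more hours a week in the last month. Over the past six months D requires fewer than 20 hours and E requires no more than 19. For whole hours, fewer than 20 and at most 19 are the same set. The two differ only between 19 and 20 hours and in their opening words.

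**Step 2: truth table.** Take 10 hours a week to stand for play below the threshold and 30 for play above it. The periods are the last month, months 2 to 6 back (peak), and any earlier time (peak). The loose reading takes D to mean that at some time in the past six months play was under 20 hours.

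| Last month | Months 2–6 back | Earlier | True options, literal | True options, D read loosely |
|---|---|---|---|---|
| 10 | 10 | 10 | D, E, F | D, E, F |
| 10 | 10 | 30 | D, E | D, E |
| 10 | 30 | 10 or 30 | none | D |
| 30 | 10 or 30 | 10 or 30 | A, B or C | A, B or C |

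The third row is the adolescent who has recently cut down.

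**Step 3: timing.** Time since the sessions start = 2 months + follow-up.

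- 1-month follow-up: 2 + 1 = 3 months.
- 3-month follow-up: 2 + 3 = 5 months.

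Both are less than 6. An adolescent at 20 or more hours up to baseline who later drops below it is therefore in the third row at both follow-ups.

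**Step 4: the model.** The SOCQ is a secondary outcome, and linear models are stated for the secondary outcomes. The protocol names no ordinal or categorical model.

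**Step 5: effect of correcting D.** Suppose D required under 20 hours in the last month but 20 or more at some time in the past six months. The third row would then give D alone, the second E alone, and the first E and F, of which F is the more specific.

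**The case against.** The best reply is that this is loose English for a sound item. D opens with a contrast, which suggests that heavier play earlier in the six months was intended. A respondent who has cut down may well understand it that way and choose D. The item is attributed to a cited source, and neither that source nor the wording shown in the app is in the article. Much of this stands: a slip in wording or translation is the likeliest explanation, and the source should be consulted first. It does not remove the overlap, because the reading of D that admits those who cut down also admits everyone in E and F.

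It can also be said that one summary sentence in a condensed article need not govern how a single-item measure is analysed, and that an analysis plan may refine it. That is fair as to weight. The sentence is nevertheless a positive statement covering all secondary outcomes, not a silence.

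Three stronger readings are tempting, and the documents do not support them:

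- A reader might infer that option E will wrongly record as Maintenance those who cut down during the trial. Read literally, E excludes them: at 3 or 5 months their play above 19 hours still lies within the past six months. E agrees with the six-month definition of Maintenance, and the fault lies in D.
- A reader might infer that a mean of codes 1 to 6 will be analysed. The protocol assigns no numbers to the options, and it keeps F apart from the five stages.
- A reader might infer that F contradicts the entry score of 32 or more. The IGDS-SF9 scores symptoms, and the eligibility criteria set no threshold for hours, so an eligible adolescent could truthfully answer F.

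**Conclusion.** The point holds as a defect of wording together with a poorly matched analysis. As printed, Action and Maintenance share one condition. On the literal reading, those who cut down from 20 or more hours have no matching option at either follow-up. On the loose reading they have D, but D no longer distinguishes them from respondents in E or F. Neither reading yields a usable split between D and E.

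The number of participants affected cannot be computed from the article, because weekly hours are not an entry criterion and no baseline distribution of hours is given. The conclusion assumes that the printed options match what participants see and that hours are reported as whole numbers. The damage is confined to one secondary outcome and to conclusions drawn from it about stage movement. The primary outcome, IGDS-SF9, and the sample size are untouched. The change should be made, but the trial's main comparison does not depend on it.

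**What to change.** 1. Compare option D with the source instrument. Correct it so that it describes play of 20 or more hours a week at some time in the past six months but not in the last month. Confirm that the wording in the app says the same.
2. Replace the linear model for this outcome with a multilevel ordinal (cumulative-logit) model on A to E. Alternatively, analyse Action-or-later (D or E) versus earlier (A, B or C) with a multilevel binary model.
3. State that F is outside the stage order, and report it separately by arm and time point.

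The cost is one questionnaire line and one sentence in the analysis section. The binary version loses some information, because it ignores movement among A, B and C and between D and E. In return it does not rely on the split between D and E, so it is the safer choice if responses have already been collected with the printed wording.

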##### Decisional balance

The Decision Balance Scale consists of 24 items that cover two subscales of the pros and cons of decreasing online gaming. The Decision Balance Scale has been developed based on previous studies of smoking and weight reduction [58]. Adolescents will be asked to rate their agreements for their decision to play or to avoid playing digital games. An example of Pro questions includes “Digital games are a good way for me to relieve stress.” An example of Con questions includes, “I am unable to focus on activities that are not related to digital games.” All items are rated on a five-point Likert scale from 1 (not important) to 5 (very important). The total subscale is obtained by summing all 12 responses with a range from 12 to 60 [58].

##### Self-efficacy Scale

The Self-efficacy Scale consists of 14 items that are rated on a five-point Likert scale from 1 = (strongly disagree) to 5 (strongly agree). This scale has two subscales assessing situational confidence and situational temptations. Each subscale has 7 items. The total subscale is obtained by summing all 7 responses and the total score ranges from 7 to 35 [58].

##### Assessment of adherence

Participants’ adherence to the interventions will be assessed by calculation the length of time using the app and number of log-ins using an online database. Moreover, the online database will be used to assess each participant’s viewing of each page and time spent on it.

### Intervention fidelity

All educational content were prepared under auditing of the first author ([name]) who is a professor in the field of health psychology and behavioral change. Also, all research processes including recruitment, intervention implementation, and assessments will be conducted under his supervision.

### Ancillary and post-trial care

After completing the follow-up assessments, if any individuals have IGD, they will be referred to a psychologist to receive further necessary counseling and or treatment.

### Statistical analysis

A blinded biostatistician will analyze the data using SPSS version 25 and MLwiN version 2.27 software. An intention-to-treat analysis will be used to compare the intervention effects between the active control and intervention groups. The Kolmogorov–Smirnov test will be used to assess normality distribution of study variables. Multilevel linear models (MLMs) using a random-effects model will be conducted to compare primary and secondary outcome measures across the two groups over baseline and at 1 month and 3 months after the intervention. Within-group intraclass correlations will be calculated, and a two-level mixed model will be used with adolescents nested in time.

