## Methods/design

### Objectives

The overall aim of this trial is to determine the effectiveness of an educational intervention based on the TTM model and CBT in the treatment of online gambling addiction through an app in adolescents.

More specifically the study aims are to compare in the active control and intervention groups over time (before and one and three months after):
Stages of changeSelf-efficacyThe balance of decisional choicesThe intentions to perform preventive behaviors relating to online gamingLevels of stress, anxiety and depressionIGD severityGaming durationSleep health status

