After approval of the ethics Committee in Research of Qazvin University of Medical Sciences (IR.QUMS.REC.1398.358), a letter will be sent to the General Department of Education of Qazvin Province to obtain all high school lists and permission to conduct the research. The first author will hold coordination meetings with school principals and explain the research clearly. After the schools’ agreement, an announcement of the study will be posted in the schools’ channels. During the COVID-19 pandemic, a specific application (the SHAD web) was developed by the ministry of education to be used for all schools for teaching, parental involvement, and other activities. Each school has this application. Screening questionnaires will be provided to the target group through these school information channels (i.e., the SHAD WEB). In addition, in all stages of the research, to ensure the participants' satisfaction, they will be provided with an explanation that all their answers and statements will be kept completely confidential and tracked by numbers. After reviewing eligibility criteria, eligible adolescents will complete baseline measures and then will be randomly divided into two groups (active control and intervention) as detailed above and below. The intervention group will receive an educational app (HAPPYTEEN) based on the TTM model and CBT. The intervention will be conducted weekly in eight sessions with an average duration of 30 min, while the active control group will receive an intervention on sleep hygiene. It should be noted that individual participants in both groups will be assigned a unique code as username (phone number or email) to enter the app. Initial feedback from an independent sample of adolescents found that the app was understandable and acceptable to adolescents. All participants’ activities (including opening each page, duration of reading each page, the number of logins) will be monitored and evaluated by an independent researcher to ensure adherence to treatment among participants. In the app user environment, participants can also communicate with the support team via email and phone message to share any questions, criticisms, and suggestions with an independent support team. Messages related to reminder training tips and reminders to answer weekly questions are possible through the app.

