### Participants and procedure

#### Inclusion and exclusion criteria

Inclusion criteria for eligible adolescents to enter the trial will be as follows: voluntary participation of adolescents aged 13 to 18 years; studying in Abeyek high schools; full access to a computer or laptop, tablet or smartphone; internet access; scoring 32 or higher on the nine-item Internet Gaming Disorder Scale – Short Form (IGDS-SF9) [55]; and providing consent to participate in the study by both parents and adolescents. Adolescents with mental disabilities or severe mental health-related illness (such as schizophrenia and bipolar disorder) will be excluded. Moreover, the participants will be excluded if they do not receive more than 50% of the interventional materials. The procedure of recruitment and acquiring informed consent will be done by the second author ([name]).

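### Baseline IGDS-SF9, cut at 32 by eligibility, is modelled as a third outcome occasion; using it as a covariate gives an undiluted, correctly sized and more precise comparison at no cost in participants

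*Protocol article*

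**What the plan says.** The Statistical analysis section names the method: "Multilevel linear models (MLMs) using a random-effects model will be conducted". The stated purpose of these models is "to compare primary and secondary outcome measures across the two groups over baseline and at 1 month and 3 months after the intervention", and the section adds that "a two-level mixed model will be used with adolescents nested in time". The Objectives give the same set of occasions: the aim is to "compare in the active control and intervention groups over time (before and one and three months after" the intervention. Baseline is therefore a response occasion in both places, and neither mentions it as a covariate.

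Three other statements bear on this:

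- Inclusion and exclusion criteria: entry requires "scoring 32 or higher on the nine-item Internet Gaming Disorder Scale".
- Primary outcome measure: the total can "range from 9 to 45 with higher scores indicating a higher risk of developing IGD", so eligible screening scores lie in 32-45.
- Study design: "After reviewing eligibility criteria, eligible adolescents will complete baseline measures and then will be randomly divided into two groups". Baseline therefore carries no treatment effect. The text does not say whether the screening score is reused as baseline or the scale is given again.

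**The concern.** Randomisation makes the expected arm difference at baseline zero. If baseline is one of the outcomes averaged into an arm effect, a known zero is averaged in with the two quantities of interest.

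The entry cut adds a second difficulty. It compresses the variance of the primary scale at baseline and weakens its correlation with follow-up, but does neither to the same degree between the two follow-ups. A two-level model with a random intercept, the ordinary reading of the text, assumes one variance for all occasions and one correlation for every pair. The pooled variance is then too small for the follow-up occasions.

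At stake is either the reported size of the primary effect or the validity of its confidence interval and p-value, depending on which coefficient is read. The issue is separate from the wording about which unit is nested in which, and remains when occasions are nested in adolescents.

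**Working it through.** **The plan's own figure.** A two-sided t-test at d = 0.50, 90% power and alpha 0.05 needs 86 per arm; 86 x 1.2 = 103.2, which gives the stated 103 per group. So 103 matches a single-endpoint comparison.

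**Dilution.** With the same effect d at both follow-ups and zero at baseline, the pooled arm effect is (0 + d + d)/3. For d = 0.50 this is 0.33. No assumed input is needed beyond equal effects at the two follow-ups. The pooled standard error is correct: the ratio of model to true value is 1.00.

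**Inputs for the standard errors.** The protocol gives no correlations. The pilot SD of 16.91 cannot stand in: with mean 34.59, scores confined to 32-45 have SD at most sqrt((45 - 34.59)(34.59 - 32)) = 5.2. Assumed instead: screened population mean 20, SD 8, reliability 0.85, true-score stability 0.8 from baseline to follow-up. Scores are rounded and held to 9-45, with selection at 32 or more. True-score stability between 1 and 3 months is varied over 1.0, 0.9 and 0.8. Baseline is either the screening score reused or a second administration.

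After selection, baseline SD is 3.0 (reused) or 4.9 (re-measured), against 6.2 at follow-up. The baseline to follow-up correlation is 0.34 or 0.39. The correlation between follow-ups is 0.75, 0.61 or 0.47 for the three stabilities.

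**Formulas.** Let m be the mean of the three variances, c the mean of the three covariances, and s = m - c. The random-intercept model gives these contrasts the following variances, each times 2/n:

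- follow-up difference at 3 months: m
- difference in the mean of both follow-ups: c + s/2
- change to 3 months: 2s
- change to the mean of follow-ups: 1.5s

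Type I error = 2(1 - Phi(1.96 x SE ratio)), where SE ratio = sqrt(model variance / true variance).

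**One case in full** (screening score reused, stability 0.9 between follow-ups). Variances are 9.24, 38.30 and 38.41; covariances are 6.35, 6.33 and 23.51. So m = 28.65, c = 12.06, s = 16.59.

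- 3-month difference: model 28.65, true 38.41, ratio 0.864, type I error 9.1%.
- Mean of follow-ups: model 12.06 + 8.30 = 20.36, true (38.30 + 38.41 + 2 x 23.51)/4 = 30.93, ratio 0.811, type I error 11.2%.
- Change to 3 months: model 33.18, true 9.24 + 38.41 - 2 x 6.33 = 34.99, ratio 0.974, type I error 5.6%.
- Baseline-adjusted variance at 3 months: 38.41 - 6.33^2/9.24 = 34.07, so the change score has 34.99/34.07 = 1.03 times that variance.

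**All cases** (SE ratio, type I error):

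| Baseline | Stability 1 to 3 months | Difference, 3 months | Difference, mean of both | Change, 3 months | Change, mean of both |
|---|---|---|---|---|---|
| Reused | 1.0 | 0.86, 9.1% | 0.80, 11.9% | 0.92, 7.1% | 0.86, 9.3% |
| Reused | 0.9 | 0.86, 9.1% | 0.81, 11.2% | 0.97, 5.6% | 0.95, 6.2% |
| Reused | 0.8 | 0.86, 9.1% | 0.83, 10.4% | 1.03, 4.4% | 1.05, 3.9% |
| Re-measured | 1.0 | 0.94, 6.6% | 0.87, 8.7% | 0.91, 7.4% | 0.84, 9.9% |
| Re-measured | 0.9 | 0.94, 6.6% | 0.89, 8.0% | 0.96, 6.0% | 0.93, 7.0% |
| Re-measured | 0.8 | 0.94, 6.6% | 0.92, 7.2% | 1.01, 4.8% | 1.01, 4.7% |

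The variance of the change score relative to baseline adjustment is 1.03-1.20 at 3 months and 1.03-1.28 for the mean of follow-ups.

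**Other inputs.** A second set (population mean 20 or 25, SD 8, pre-selection baseline to follow-up correlation 0.3-0.7, follow-up to follow-up 0.5-0.8, 86 evaluable per arm) gives SE ratios for the follow-up difference of 0.85-0.88 (reused) and 0.91-0.97 (re-measured), and 0.91-1.05 for change. Baseline adjustment gives 0.99-1.00, coverage of 94.5-95.0%, and power of 91-95%.

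**The case against.** The strongest reply is that no error has been shown. The contrast and the covariance are not spelled out, and such detail commonly sits in an analysis plan that is not at hand. Comparing groups over time most naturally means arm-by-time, not an arm effect averaged over a pre-treatment visit. Random-effects wording does not exclude occasion-specific variances. Baseline as an outcome is legitimate if the arms share a baseline mean and the covariance is unstructured.

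Much of this stands, and it limits the point. The silence is not the finding. What is stated is that baseline is one of the compared occasions, and each natural reading of that does worse than adjustment in effect size, in standard error or in precision.

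Four stronger readings are tempting and are not supported:

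- That the arm-effect error bars are too narrow whichever contrast is read. For the pooled effect they are correct. For change from baseline they can be too narrow, right or slightly wide.
- That the cut at 32 by itself inflates the change contrast. The cut is present in every row of the table, yet type I error falls from 7-10% to 4-5% as stability between follow-ups drops from 1.0 to 0.8.
- That selection biases the comparison. It precedes randomisation and applies to both arms.
- That the secondary scales suffer the same distortion. The cut applies to IGDS-SF9 only.

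Nor does dilution translate directly into lost power, because the pooled standard error is also smaller. In simulations from the second input set, pooled power was 80-95%, against 91-95% for the baseline-adjusted 3-month score alone.

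**Conclusion.** The point holds as a matter of analysis choice, with the harm tied to the contrast. Dilution to two thirds is certain if a pooled arm effect is reported, given equal effects at both follow-ups. Standard errors for follow-up differences are about 6-20% too small under the main inputs (3-15% under the second set), provided that the model has an equal-variance random intercept. For change from baseline the firm conclusion is lower precision, by 3-28% in variance under the main inputs. Its type I error, about 4-10%, turns on a correlation that the documents do not supply. Dilution and understated standard errors fall on different contrasts and should not be added together. The amendment is worth making because it improves the primary analysis under every one of these readings.

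**What to change.** Replace the model sentence in the Statistical analysis section with wording such as: the 1-month and 3-month scores are the outcomes; the model contains arm, time, arm-by-time and the pre-randomisation score of the same scale as covariate, with an unstructured covariance between the two follow-ups.

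An equally valid alternative keeps baseline as an outcome but constrains the arms to a common baseline mean, with an unstructured 3x3 covariance. This version also retains adolescents who have a baseline but no follow-up score, which suits the intention-to-treat aim. The constraint must not be adopted without the covariance: with only a random intercept, SE ratios were 0.80-0.96 and coverage 88-94%.

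Use the same form for the secondary scale scores, giving precision as the only reason.

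The cost is analysis wording and a few extra variance parameters. The baseline score is already collected, and no new data or participants are needed. The required number does not rise: with r the baseline to follow-up correlation in the selected sample (assumed), 86(1 - r^2) is 83 per arm at r = 0.2 and 65 at r = 0.5, before allowance for loss.
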